## Methods

### Study Goals

The purpose of this study is to investigate the efficacy of an evidence-based system of SMS messages linked to accurately measured BP in the community. The individual BP measurements are taken by community health workers (CHWs). This innovation allows for transmission of accurate BP measurements from patients in isolated or underserviced populations to health care providers and, subsequently, improvement of patient knowledge about hypertension management. Participants in the Dream-Global study are randomized to receive either SMS messages that are both active and passive, compared with those receiving only passive messages. All messages are derived from the Hypertension Canada Clinical Practice Guidelines and are subsequently modified with community input to make them culturally sensitive and specific in both Canada and Tanzania [25]. The 12 active messages explain the importance of BP control, describe the rational for medical therapy, and, based on the BP reading, may instruct the participant to contact their health care provider for further BP follow-up. The 26 passive messages include health behaviors change advice for diet and exercise. Messages are sent twice weekly, on Monday and Thursday at 11 AM (to avoid holidays). The study is divided into five projects that involve the design, implementation, and then staging of the research program for the successful execution of a randomized controlled trial in both Canada and Tanzania.

*Project 1* is to develop a readiness to participate tool. The tool entails a multidimensional checklist intended to assess community readiness for implementation of a research program for hypertension awareness, treatment, and control. The tool developed was piloted in both Canadian Indigenous and Tanzanian communities participating in the Dream-Global study with evaluation and feedback for validation [24].

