### Blood Pressure Screening: Canada

In the Canadian Indigenous communities, the community nurse and CHR, a nonmedical health worker (analogous to CHWs in Tanzania), was trained in all aspects of the study, including BP measurement with the automated device, how to recruit, and how to consent participants. Consent was obtained from all participants, including the CHR, community nurse, and other members of the health care team and Band leadership who participated in surveys and interviews, as well as all participants for the BP measurement and lowering study.

Community leadership recommended that all interested individuals be allowed to participate as long as they are eligible. The study initially had focused on BP lowering, but to meet the community needs, a BP finding substudy was expanded to allow participants who were medically untreated but who screened below enrollment thresholds to participate. The screening BP was measured by trained Home and Community Care nurses or CHRs in community clinics using the BpTRU (BpTRU Medical Devices Ltd, Coquitlam, British Columbia, Canada), which takes six readings, omitting the first and averaging the final five. This BP reading, along with the participant’s baseline demographics, was recorded on a data collection form, which was deidentified and faxed back to the study center. Participants for the BP lowering study had to have uncontrolled hypertension while being on or off medications. Uncontrolled hypertension was defined as 140/90 mm Hg or above, or 130/80 mm Hg or above for participants with diabetes. In this way, only people on medications and who had BP controlled to target were not eligible. By limiting subjects who were ineligible for ongoing BP monitoring and SMS messages, the study met the needs of the community. It was recognized that some subjects who appeared to have controlled BP at screening might turn out to be uncontrolled and that some who appeared to be uncontrolled at screening might later turn out to be controlled.

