Eligible participants were registered online. At registration, they were randomized electronically to receive active and passive SMS messages or passive only, and their names were then listed on the Dream-Global mobile app on the smartphone used by the Home and Community Care nurse or CHR in their community. BP was measured with the A&D UA-767PBT-C monitor (A&D Medical, San Jose, CA) to test that it was being transmitted properly; an SMS message to the participant’s registered mobile phone, with the BP reading, was the confirmation of transmission. The Home and Community Care nurse and CHR were trained to take three BP readings with this device. The study server was programmed in such a manner that it waits for up to three readings and then sends their mean to the participant’s own phone. Randomization through the study server ensured that participants and study personnel were blind to the allocation.

The baseline BP was defined as the mean of all readings from the A&D device in the first 2 months after randomization. If the average BP was uncontrolled during the first 2 months, the patient was identified as being in the BP lowering study; otherwise, they were followed up for BP screening. BP readings were stored on the central server, and deidentified data were transferred monthly to the data analysis center in Ottawa.

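### Both the BP lowering population and the baseline of the change score are set by BP measured in the 2 months after randomization, so any early effect of the active messages biases the primary comparison, mainly toward no effect

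*Protocol article*

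**What the plan says.** All of this is in the protocol article.

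- **Randomization (Blood Pressure Screening: Canada).** "At registration, they were randomized electronically to receive active and passive SMS messages or passive only". Blinding and Randomization also places allocation at enrollment.
- **Baseline (same section).** "The baseline BP was defined as the mean of all readings from the A&D device in the first 2 months after randomization". The section on primary and secondary outcomes repeats this window and gives regression to the mean as the reason.
- **Population (same section).** "If the average BP was uncontrolled during the first 2 months, the patient was identified as being in the BP lowering study". Everyone else goes to the screening part of the program.
- **Thresholds (same section).** "Uncontrolled hypertension was defined as 140/90 mm Hg or above, or 130/80 mm Hg or above for participants with diabetes".
- **Screening (same section).** A BpTRU value, the average of five readings, is recorded on the data collection form before registration. The text expects that "some who appeared to be uncontrolled at screening might later turn out to be controlled", and the reverse.
- **Exposure.** "Messages are sent twice weekly, on Monday and Thursday at 11 AM" (Study Goals). The app requirements, printed under Knowledge Translation and Engagement, add that a high reading triggers advice to see the provider in the active arm only.
- **Primary outcome.** The between-group difference in BP change from baseline to study end, defined for the BP control study. I read this as the BP lowering study.
- **Analysis set (Statistical Analysis).** At least one message and one follow-up reading. Nothing says that people reassigned to screening remain in the primary comparison.

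**The concern.** Membership of the primary population and the starting point of the change score both rest on a variable that the intervention is meant to change. If active messages act within 2 months, two things follow.

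1. **Selection.** Some active participants fall below threshold who would have stayed above it on passive messages alone. They leave the primary comparison and their passive counterparts do not. The active participants who remain had higher BP before randomization.
2. **Baseline contamination.** The change score starts from a BP already lowered by treatment, so the early part of the effect is subtracted from the estimate.

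At stake are an understated effect and lost power, in a program that enrolled 234 people with transmitted readings against a target of 360. Adjusting for the 2-month mean would not help, because that mean is itself affected by treatment.

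**Working it through.** **1. The plan's own figure.** Sample Size gives a diastolic difference of 4.8 mm Hg, SDs of 10.6 and 11, inflation factor 1.1729, 176 per group and 97% power. Pooled SD = √((10.6² + 11²)/2) = 10.80. Effective n = 176/1.1729 = 150 per arm. At two-sided alpha 0.05 (not stated, assumed), power is 97.1%. The figure reproduces, but it presumes that the full 4.8 mm Hg is estimated.

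**2. Systolic illustration.** Assumed, not in the document: usual systolic BP of mean 145 and SD 12; error SD 6 for each measured mean; threshold 140; the same effect δ for everyone, with a fraction f of it present in the 2-month mean. I take δ = 7 (the systolic difference in the earlier DREAM3 study, quoted in Sample Size) and δ = 2 (the smallest difference that section calls important).

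The SD of the 2-month mean is s = √(12² + 6²) = 13.42. With e = 0 in the passive arm and e = fδ in the active arm:

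- z = (145 − e − 140)/s; proportion retained = Φ(z); λ = φ(z)/Φ(z)
- pre-randomization mean of those retained = 145 + (144/s)λ
- 2-month mean of those retained = 145 − e + sλ

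Passive arm: z = 5/13.42 = 0.373, retained 0.645, λ = 0.577, pre-randomization mean 151.19, 2-month mean 152.74.

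Active arm, δ = 7, f = 0.5: z = 1.5/13.42 = 0.112, retained 0.5445, λ = 0.728, pre-randomization mean 152.81, 2-month mean 151.27.

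- Pre-randomization imbalance: 152.81 − 151.19 = 1.6
- Difference in final BP: 7 − 1.6 = 5.4
- Difference in 2-month means: 152.74 − 151.27 = 1.5
- Difference in change: 5.4 − 1.5 = 3.9
- Difference in change with the same baseline but no selection: δ(1 − f) = 3.5

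| δ | f | Retained, passive v active | Imbalance | Final BP difference | Change difference, rule as written | Change difference, no selection |
|---|---|---|---|---|---|---|
| 7 | 0.25 | 65% v 60% | 0.8 | 6.2 | 5.4 | 5.3 |
| 7 | 0.5 | 65% v 54% | 1.6 | 5.4 | 3.9 | 3.5 |
| 2 | 0.25 | 65% v 63% | 0.2 | 1.8 | 1.6 | 1.5 |
| 2 | 0.5 | 65% v 62% | 0.4 | 1.6 | 1.1 | 1.0 |

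A simulation with 2,000,000 people per arm agrees. With f = 0, retention is equal and the full δ is recovered.

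**3. Which defect does what.** On the protocol's endpoint the last two columns are close, so the shrinkage comes mainly from the on-treatment baseline. Under a uniform effect, selection even offsets a little of it. What selection itself does shows in the imbalance and in the final BP difference.

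**4. Diastolic check on the plan's 4.8 mm Hg.** Assumed: mean 90, SD 8, error SD 5, and both screening and 2-month values at or above 90. With 25%, 50% or 75% of the effect early:

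- Retained: about 75.5% of passive against 70%, 65% or 58% of active participants.
- Change difference: 3.9, 2.9 or 2.0 mm Hg. Power with effective n held at 150 per arm: 87%, 65% or 36%.
- Baseline contamination alone, 4.8(1 − f): 3.6, 2.4 or 1.2.
- If individual effects vary with SD 5, the rule gives 3.5, 2.4 or 1.4; with SD 8, 3.1, 1.7 or 0.7. Selection adds clear loss on the change score only when responses vary widely.

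**5. The remedy in the systolic model.** Selecting on screening BP at or above 140 and regressing final BP on arm and screening BP returns 7.0 and 2.0 mm Hg. Changing the population alone and keeping the 2-month baseline gives only 5.25 and 3.5 for δ = 7 (f = 0.25 and 0.5).

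**The case against.** The rule is the same in both arms, readings are taken blind to allocation, and the 2-month baseline has a stated purpose. Both arms receive passive messages and their own BP readings, so the contrast may be far smaller than the 7 mm Hg seen when a nurse was added to usual care. The date of the first message is not given, and no early-effect figure appears in the document.

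Much of this stands. Bias needs a difference between active and passive messages inside the 2-month window. Early exposure is an inference from randomization at registration, twice-weekly sending and the advice after high readings; no run-in or delayed start is described. At 2 mm Hg the retention gap is only 1 to 3 percentage points. But blinding does not stop selection by a treatment effect. Regression to the mean falls equally on both arms when selection uses a value from before randomization, so the stated purpose does not require this rule.

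A reader might infer three stronger points that the documents do not support:

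- **That the text contradicts itself**, because it also says "Participants for the BP lowering study had to have uncontrolled hypertension while being on or off medications" in the screening paragraph. That paragraph goes on to expect reclassification, so the two statements form one two-step scheme.
- **That only the active arm loses responders.** Both arms do; the harm is the differential loss.
- **That false positives are at risk.** If active messages have no effect, retention is balanced and type I error is not inflated.

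**Conclusion.** The point holds: the population and the baseline of the primary comparison are both defined after randomization, and no other section cures this. The expected direction is mainly toward no effect. For a 7 mm Hg systolic effect with a quarter to a half present early, the estimated change difference falls to 5.4 to 3.9 mm Hg; for 2 mm Hg, to 1.6 to 1.1. Most of that is baseline contamination. Selection adds a pre-randomization imbalance of 0.8 to 1.6 mm Hg at the larger effect and 0.2 to 0.4 at the smaller. These sizes rest on assumed BP distributions and early-effect fractions. That some bias arises depends only on active messages acting within 2 months.

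**What to change.** Change population and baseline together:

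- Define the BP lowering population by the BpTRU screening BP recorded before randomization, using the thresholds already in the article.
- Analyse everyone so defined in the arm randomized, with final A&D BP as outcome and screening BP as covariate.
- Report the 2-month definition of population and baseline as a sensitivity analysis only.

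The cost is analysis wording, since the screening BP was collected. Follow-up ended in December 2016, so the change should be settled before the arms are compared. The downsides are small: screening is a single session on a different device from the endpoint, some people with transiently raised readings come in, and some who were controlled at screening but uncontrolled later are left out. Each of these falls equally on both arms.

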### Blood Pressure Screening: Tanzania

A 6-week BP screening exercise in Tanzania was used as training to test the technology and the operationalization and feasibility of the protocol implementation in the participating rural communities in Kilimanjaro, Tanzania. CHWs were trained to utilize an Android smartphone with the study app. All eligible participating members were invited to participate in the BP screening study to measure community interest.

### Canada-Specific Considerations

The Canadian arm of the project was carried out in six Indigenous communities located in three different geographic regions, including Ontario’s Manitoulin Island, the James Bay Coast of Quebec, and the north shore of New Brunswick. Recruitment into the study began in the spring of 2013 and was completed by November 2015. The last patient exited the study at the end of 2016. Study participants were followed for a period of at least 1 year. Communities were selected through a semirandom method. Canadian Indigenous communities can be found on an interactive map maintained by the Government of Canada with profiles, including population information [28]. Potential communities included those with a population of at least 3000, existing 3G mobile phone service, stable governance, and a clinical champion to serve as a bridge between the Dream-Global study researchers and the community. Potential communities were listed and put into a random order. They were contacted one by one until it was felt that sufficient communities had been contacted to make the planned study enrollment. Communities were later assessed with the Intervention and Research Readiness Engagement and Assessment of Community Health Care (iRREACH) tool (see below) to determine their readiness for research and the necessary study adaptations required to meet their needs [24].

Following an invitation by the community to discuss the study, a visit was arranged with the Canadian study lead (ST) and study staff (NP) to introduce the Dream-Global research program. This was followed by another visit to determine research readiness with the iRREACH community research participation tool [24]. A Band or Tribal Council resolution was required to ensure that the study was endorsed by the community leadership. This was particularly important because the nonmedical worker, or CHR, was central to the functioning of the study. The CHR was not compensated by the study but rather by the community who felt that the study was of sufficient importance, including research capacity development to provide enough of the CHR’s time to manage hypertension (typically 1 day per week).

The CHRs participating in the study in each community were identified by the community leadership. The CHR worked closely with a Home and Community Care nurse, and both were trained by the Dream-Global study staff to perform the BP measurements, to recruit, consent, and enroll study participants. The training took place over a period of 2 days and was conducted by one of the Dream-Global staff (NP). The training manual was developed with input from the communities and was designed to be culturally safe. As needed, weekly teleconferences were held between the CHRs, the Home and Community Care nurse, and the Dream-Global study team. These sessions were used to troubleshoot challenges with the technology, recruitment strategies, and BP management. The CHR or the Home and Community Care nurse were aware of the BP readings but were instructed not to act on them unless the readings were 180/100 mm Hg or higher or the participant appeared to be in distress. Every effort was made to get medical attention for the participant on an escalating scale based on the BP reading through the local health care system, even to the point of activating the local emergency medical system. Study staff were available at all times through their personal mobile phones via SMS texting or direct calls. Focus groups and key informant interviews were undertaken at the beginning and end of the study to understand the health team’s response to the Dream-Global technology. Exit interviews were arranged for participants, including a knowledge test of the content of the SMS messages.

### Pragmatic Aspects of the Randomized Controlled Trials

Pragmatic randomized controlled trials (RCTs) are designed to evaluate an intervention in real-life routine practice conditions in contrast to traditional explanatory RCTs that operate in optimal conditions [29]. When working with Indigenous community–based health research, including community engagement and community involvement in the design and study implementation, a pragmatic RCT supports data collection in a respectful and participatory way. It can determine whether the intervention is effective and works in a real-life setting. The Dream-Global study was designed to be a pragmatic study to meet the needs of the participating communities, to provide the ability to do a process evaluation to understand the ultimate study results, and to increase the probability that evidence from the study could be used in clinical practice and policy [30].

### Eligibility Criteria

#### Inclusion Criteria

Inclusion criteria were as follows: age 18 years or older and a diagnosis of hypertension for at least 12 weeks before screening. If already on drug therapy, continuation of the same dosing interval for 8 weeks before the screening for BP. Participants must be able and willing to provide written informed consent, possess a mobile phone capable of receiving SMS text messages, or, for those in Canada with no phone, willing to carry and learn to use a flip phone for the study duration.

#### Exclusion Criteria

People who meet the eligibility criteria for either of the above studies but have poorly controlled hypertension (BP>180/110 mm Hg), have an active malignant disease (except nonmelanoma skin cancer), are planning elective surgery during the study period (except for cataracts), are participating in another clinical trial, do not have a primary health care practitioner, are unable or unwilling to visit a health care provider, and/or are unable to read the SMS messages are ineligible for study participation. People on investigational drugs (in the 3 months before initial screening visit or during screening and treatment periods) or using SMS-related interventions (in the 12 weeks before screening or during screening and treatment periods) are also ineligible.

### Local Health Provider Engagement and Support

In Canada, a continuing professional development information session was made available for local primary health care practitioners on the Dream-Global research program and hypertension clinical practice guidelines were updated. These sessions were held at least once for each region and took place on reserve or close to the reserve. In addition to the extensive training on the Tanzanian Standard Treatment Guidelines for Hypertension (2013) provided to the local health providers at the participating health centers, the research team in Tanzania collaborated with a local referral hospital to host an event on updated hypertension treatment guidelines and cardiovascular disease management.

### Sample Size

For BP lowering, a reduction in systolic BP of 5 mm Hg is associated with a 14% reduction of stroke, a 9% reduction of coronary heart disease mortality, and a 7% reduction in total mortality; even reductions of 2 mm Hg are associated with significant benefits (−6%, −4%, and −3%, respectively) [28]. Thus, a significantly important difference could be as low as a 2-mm Hg change in systolic BP. In the DREAM3 study groups, systolic BP changed by mean 24.0 (SD 13.5) mm Hg and 17.0 (SD 18.6) mm Hg, with a between-groups difference of 7 mm Hg. Using the more conservative change in diastolic BP from that study, with mean 11.6 (SD 10.6) mm Hg versus 6.8 (SD 11) mm Hg in the control group (mean difference 4.8 mm Hg), provides an intraclass correlation coefficient for BPs between groups of 0.0133. This translates to an inflation factor of 1.1729 with 176 subjects per group for power of 97% to find the difference. Thus, a target was set for 360 participants to be recruited. The extra power was built in to allow for underrecruitment and a smaller difference in BPs between the groups.

The BP finding study is run as a pilot to determine the role of the Dream-Global program to identify the new onset of hypertension.

### Blinding and Randomization

Participants were randomly allocated after enrollment using random number sequence with blocking of 2s and 4s for each community so that participants and study staff would not know which group participants had been enrolled. The randomization to receive active and passive or passive only text messages took place at the time of enrollment by the central server software. This information was available only to the database manager; participants, clinicians, and study staff had no knowledge of randomization.

### Participant Flow

Canadian community members were invited to participate in the study through local advertisements and community engagement (town hall meetings and messages from the Band leadership). Referrals were also expected to come from all community health practitioners and Band leadership.

After enrollment, all BPs are measured with the A&D Bluetooth-enabled BP device by the CHR or Home and Community Care nurse in Canada or the CHW in Tanzania. Canadian participants typically meet the CHR in their office in the Band Council’s health facility on reserve. In Canada, all consent forms were in English but could be translated for participants by the CHR if necessary. In Tanzania, all study information and consent forms are pretranslated into Swahili.

Attempts were made to discourage people living in the same house from enrolling in the study to reduce the potential for cross contamination between the messages. However, to respect the community leadership in both countries to make participation widely available, this could be overruled by the CHRs and CHWs if they felt it was necessary.

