*Project 2* is a substudy to determine whether the sodium consumption of Indigenous people can be modified to help prevent hypertension. The goal was to plan and implement a food procurement policy for reducing sodium and fat intake from commercial food sources in an isolated Northern Indigenous community. This was approached by collating scientific evidence and existing policy recommendations, engaging community leaders and local food suppliers, and developing a policy approach for commercial food procurement practices. Evaluation includes process measures and examination of successes and barriers to implementation.

*Project 3* entails the development of a closed loop app to transmit BP results taken by the CHR in Canada and the CHW in Tanzania to the health care provider and to the participant in a manner consistent with personal health privacy rules in each country.

*Project 4* includes the development of a guidelines-based set of SMS messages in English that are culturally appropriate for Canadian First Nations communities and a set of SMS messages in Swahili that are culturally specific and appropriate for rural Tanzanian communities.

*Project 5* will evaluate the impact of the active and passive messages together, compared with that of passive messages alone on BP control over 1 year through a prospective, pragmatic, randomized controlled trial in both Canada and Tanzania.

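### Housemates may be co-enrolled and are then randomised one by one, so about half to two thirds of such pairs would be split between arms, with possible dilution of the contrast toward zero

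*Protocol article*

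**What the plan says.** Under Participant Flow, the protocol article says that people living in the same house were discouraged from enrolling "to reduce the potential for cross contamination between the messages". The next sentence relaxes this: because community leaders in both countries wanted participation to be widely available, "this could be overruled by the CHRs and CHWs if they felt it was necessary". No criterion or limit for an override is stated.

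Under Blinding and Randomization: "Participants were randomly allocated after enrollment using random number sequence with blocking of 2s and 4s for each community". The central server does this at enrolment. The unit is the individual, and nothing links the allocation of two people from one household.

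Under Study Goals, Project 5 evaluates active and passive messages together "compared with that of passive messages alone on BP control over 1 year". There are 12 active messages. They explain why BP control matters and the reasons for drug treatment and, depending on the reading, may tell the participant to contact a provider. The 26 passive messages give diet and exercise advice. Both arms have community BP measurement and receive their readings by text.

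The Sample Size section says that extra power was included to allow for under-recruitment and for a smaller difference between groups. It does not mention household sharing.

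**The concern.** The article names the contamination route and then lets field staff set aside the only safeguard against it, and allocation does not respond when they do. Overrides are plausible: the section on BP screening in Canada reports that community leaders wanted every interested and eligible person to be able to join.

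This contrast is more exposed than a comparison with usual care would be, because the whole difference between arms is text content that can be read aloud or shown on a phone. The active arm already receives the passive messages, so it gains nothing from a passive-arm housemate. A passive-arm participant who sees a housemate's active texts gets part of the intervention under test. If the active messages work, such sharing can only reduce the observed difference.

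**Working it through.** **1. The plan's own figure.** Inputs from Sample Size: diastolic difference 11.6 − 6.8 = 4.8 mm Hg, SDs 10.6 and 11, intraclass correlation 0.0133, inflation factor 1.1729, 176 per group, power 97%. A two-sided 5% level is assumed, as none is stated there.

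- Pooled SD = √((10.6² + 11²)/2) = 10.80.
- The two-sample formula at 97% power gives 150 per group; 150 × 1.1729 = 175.9, so 176. The figure is reproduced.
- 1 + (14 − 1) × 0.0133 = 1.1729, so the factor implies clusters of 14. It inflates variance and makes no allowance for a diluted effect.

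**2. Chance that two housemates are in opposite arms.** Two places in the same block of 2 always differ; two in the same block of 4 differ with probability 2/3; two in different blocks differ with probability 1/2. Back to back:

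- Blocks of 2 only: (1 + 0.5)/2 = 75%.
- Blocks of 4 only: (3 × 2/3 + 0.5)/4 = 62.5%.
- Equal mix (assumed; the article does not give the mix): (1 + 3 × 2/3 + 2 × 0.5)/6 = 67%.

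With an equal mix and other people registered in between:

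| People between | Formula | Opposite arms |
|---|---|---|
| 0 | as above | 67% |
| 1 | (2 × 2/3 + 4 × 0.5)/6 | 56% |
| 2 | (1 × 2/3 + 5 × 0.5)/6 | 53% |
| 3 or more | always different blocks | 50% |

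Simulation agrees (66.6%, 55.7%, 52.7%, about 50%). Simple randomisation would also give 50%. The main cause is therefore individual allocation without a household rule; the small blocks add to it only for housemates who register close together.

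**3. Dilution.** Let h be the share of passive-arm participants living with an active-arm participant, and c the fraction of the effect they pick up. The expected difference is multiplied by 1 − h × c. The article gives neither quantity, so both are assumptions.

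- h = 10%, c = 0.5: factor 0.95; 4.8 becomes 4.56 mm Hg.
- h = 20%, c = 1: factor 0.80; 4.8 becomes 3.84 mm Hg.

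In households of two, h is the share of participants with an enrolled housemate times the chance of opposite arms. So h of 10 to 20% needs from 10/0.667 = 15% to 20/0.5 = 40% of participants to have an enrolled housemate.

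**4. Power at those differences**, using the plan's inflation factor. The second row takes the 234 reported under Results, split equally and all assumed to be in the BP lowering analysis, which is optimistic.

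| Per group | No loss | 5% lost | 20% lost |
|---|---|---|---|
| 176 | 97% | 95.5% | 87% |
| 117 | 88% | 85% | 71% |

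**The case against.** The risk is disclosed, partly mitigated and knowingly traded against the communities' wish for open participation in a pragmatic trial. Sample Size makes a general allowance for a smaller difference. Messages go to each participant's own phone, and the advice to see a provider is triggered by that participant's own reading, so a housemate's texts do not replace it. Complete uptake (c = 1) is therefore an upper bound. The upper values of h also require a good deal of co-enrolment despite the discouragement.

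All of this stands and limits the size of the problem. It does not remove it. The general texts on BP control and treatment can still be shared, about half of co-enrolled pairs would be split whatever the order of registration, and the power allowance was tied to a target of 360 while Canada enrolled 234.

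A reader might go further in four ways that the document does not support:

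- *Housemates usually land in opposite arms.* This is true only for those registered back to back or nearly so, and the article says nothing about registration order.
- *Messages were shared and the result is biased.* The article speaks only of a potential and reports neither co-enrolment nor sharing.
- *A null result could not be interpreted.* A loss of 5 to 20% does not go that far, and the drop from 97% to 88% power at 117 per group comes from enrolment alone.
- *Housemates comparing texts breaks the blinding.* Seeing different texts does not by itself show which set is under test, and BP is read by an automated device.

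**Conclusion.** The point holds as a weakness of the stated design: co-enrolment within a household is permitted, allocation is individual, and no household rule applies. Between 50% and 67% of co-enrolled pairs would be split, the upper figure resting on back-to-back registration and an equal mix of blocks of 2 and 4. The direction of any resulting bias is clear, toward no difference. Its size cannot be derived from the article; the 5 to 20% loss is an illustration under assumed h and c, and the true loss is small if co-enrolment was rare. The point is worth acting on because the correction is cheap, but it is no ground for dismissing the trial's result.

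**What to change.** Keep the communities' override.

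**Where randomisation is still to come.** The Objectives section says that the Tanzanian part was delayed and that a fuller protocol is in preparation. If that protocol has no household rule, add one: record household at registration, and have the server give any later member the first registrant's message set. Keep all members in the primary analysis, as the Statistical Analysis section's inclusion rule implies, and cluster standard errors by household. Restricting the primary analysis to first registrants is not advisable. It departs from that rule and, with 15 to 40% of participants in pairs, would discard half of them, 7.5 to 20% of the sample.

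**Canada, where allocation is complete.** Use the list of names and home addresses described under Knowledge Translation and Engagement to flag co-enrolled households, subject to the principles under Privacy and Cultural Considerations. Before results by arm are seen, specify a sensitivity analysis excluding households with members in both arms. Each split pair removes one person per arm, so balance is kept. Report how many households were co-enrolled and how many were split.

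**Cost.** One registration field and one server rule. With 20% of participants in pairs and an assumed household intraclass correlation of 0.1 to 0.3, the design effect is 1 + 0.2 × 0.1 = 1.02 to 1 + 0.2 × 0.3 = 1.06, and power at 176 per group stays at about 96 to 97%. A later member's arm follows the first member's, but this matters little because staff do not know the first allocation. In Canada the cost is the record linkage. With 20% in pairs, the sensitivity analysis would drop 0.2 × 0.5 = 10% to 0.2 × 0.667 = 13% of participants, about 23 to 31 of 234.
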